# The effectiveness and cost-effectiveness of 3- vs. 6-monthly dispensing of antiretroviral treatment (ART) for stable HIV patients in community ART-refill groups in Zimbabwe: study protocol for a pragmatic, cluster-randomized trial

**DOI:** 10.1186/s13063-018-2469-y

**Published:** 2018-01-29

**Keywords:** HIV, Antiretroviral treatment, Multimonth dispensing, Extended dispensing interval, Community ART-refill groups, Zimbabwe, Effectiveness, Cost-effectiveness, Cluster-randomized trial, Sub-Saharan Africa

## Abstract

**Background:**

Sub-Saharan Africa is the world region with the greatest number of people eligible to receive antiretroviral treatment (ART). Less frequent dispensing of ART and community-based ART-delivery models are potential strategies to reduce the load on overburdened healthcare facilities and reduce the barriers for patients to access treatment. However, no large-scale trials have been conducted investigating patient outcomes or evaluating the cost-effectiveness of extended ART-dispensing intervals within community ART-delivery models. This trial will assess the clinical effectiveness, cost-effectiveness and acceptability of providing ART refills on a 3 vs. a 6-monthly basis within community ART-refill groups (CARGs) for stable patients in Zimbabwe.

**Methods:**

In this pragmatic, three-arm, parallel, unblinded, cluster-randomized non-inferiority trial, 30 clusters (healthcare facilities and associated CARGs) are allocated using stratified randomization in a 1:1:1 ratio to either (1) ART refills supplied 3-monthly from the health facility (control arm), (2) ART refills supplied 3-monthly within CARGs, or (3) ART refills supplied 6-monthly within CARGs. A CARG consists of 6–12 stable patients who meet in the community to receive ART refills and who provide support to one another. Stable adult ART patients with a baseline viral load < 1000 copies/ml will be invited to participate (1920 participants per arm). The primary outcome is the proportion of participants alive and retained in care 12 months after enrollment. Secondary outcomes (measured at 12 and 24 months) are the proportions achieving virological suppression, average provider cost per participant, provider cost per participant retained, cost per participant retained with virological suppression, and average patient-level costs to access treatment. Qualitative research will assess the acceptability of extended ART-dispensing intervals within CARGs to both providers and patients, and indicators of potential facility-level decongestion due to the interventions will be assessed.

**Discussion:**

Cost-effective health system models that sustain high levels of patient retention are urgently needed to accommodate the large numbers of stable ART patients in sub-Saharan Africa. This will be the first trial to evaluate extended ART-dispensing intervals within a community-based ART distribution model, and results are intended to inform national and regional policy regarding their potential benefits to both the healthcare system and patients.

**Trial registration:**

ClinicalTrials.gov, ID: NCT03238846. Registered on 27 July 2017.

**Electronic supplementary material:**

The online version of this article (10.1186/s13063-018-2469-y) contains supplementary material, which is available to authorized users.

## Background

Sub-Saharan Africa carries the highest burden of HIV, with approximately 70% of all people living with HIV globally found in this region [1]. In 2016, the World Health Organization (WHO) broadened its guidelines to recommend that all identified people living with HIV should initiate antiretroviral treatment (ART) as soon as possible after diagnosis, irrespective of clinical or immunological status [2]. This policy is expected to reduce AIDS-related mortality, morbidity and new HIV infections. It does, however, substantially impact already overburdened health systems in sub-Saharan Africa which need to accommodate substantially increased numbers of ART patients at a time when resources for HIV are constrained globally and there is a severe shortage of professional health workers [3, 4]. An important component of the current research agenda is the development of systems that improve the efficiency of healthcare delivery by reducing unnecessary burdens on the healthcare system and better serve the needs of the large numbers of people living with HIV [5].

To realize the benefits of lifelong ART, high levels of adherence and retention are required. Barriers to adherence and retention include long waiting times at ART clinics, cost of travel to clinics, and life events that cause treatment interruptions [6–9]. Needing to frequently collect ART refills (every 1–2 months) may lead to suboptimal adherence and disengagement from care due to the time and cost to patients of frequent clinic visits, particularly for those who have to travel long distances [10, 11]. Frequent clinic visits also place a high demand on the healthcare system due to the costs of providing personnel and infrastructure. Modeling has shown that reducing the frequency of clinic visits for stable patients is expected to be cost-effective in sub-Saharan Africa [12]. Clinics that are decongested of stable ART patients may also find place to increase the rate of new ART initiations and thus scale up ART coverage [13].

Observational research in Zambia has shown that 2- and 3-monthly visit intervals were associated with decreased loss to follow-up (LTFU) and decreased visit lateness compared to patients who attended monthly [14]. A recent systematic review found that reduced frequency of clinic visits and medication pick-up for ART patients may lead to improvements in program retention and patient outcomes [15]. As a result, the WHO has recommended that stable ART patients require less frequent medication pick-ups and clinic visits (3- to 6-monthly) [2, 5]. However, the available data is sparse and the quality of evidence is “very low to low due to bias” [15]. A single, pilot cluster-randomized trial that included a comparison of clinic visit frequencies (maximum 3-monthly) for ART patients has been conducted in low-income settings, but included only 96 participants in the intervention group [16]. No larger-scale randomized trials have been conducted, and little cost data is available.

In Zimbabwe, almost 1.5 million people require ART and the country initiated more than 9000 people on ART each month in 2015 [17]. The Zimbabwe Ministry of Health and Child Care (MOHCC) has suggested that innovative strategies are required to achieve ART program goals without overwhelming the health system and to maintain a quality service [7]. Community ART-refill groups (CARGs) are a novel strategy that has been introduced with the intent to reduce barriers to patients accessing regular treatment and to limit health facility congestion [18]. CARGs are groups consisting of 6–12 stable ART patients who meet at a community venue to receive ART refills, and who provide mutual support to each other. Retrospective observational studies of community groups receiving monthly ART refills have shown encouraging results [19, 20]; however, no randomized trials have been conducted investigating prolonged ART-dispensing intervals within CARGs. Implementation research is needed to inform on the expected benefits of differentiated care models for stable ART patients in terms of their clinical and cost-effectiveness [5].

The aim of this study is to compare the clinical effectiveness and cost-effectiveness of three models of ART provision for stable ART patients in Zimbabwe, with medication pick-ups extended up to 6 months. The objectives are to measure patient retention, virological suppression, acceptability and provider and patient costs amongst stable patients who receive ART at 3- and 6-monthly intervals within CARGs. These groups will be compared to standard of care, facility-based, 3-monthly ART delivery.

## Methods

### Study design

This study is a pragmatic, three-arm, parallel, unblinded, cluster-randomized non-inferiority trial using stratified randomization with 24 months of participant follow-up. This trial is operational research based on the Zimbabwe Operational Service Delivery Manual for HIV prevention, care and treatment which outlines guidelines for differentiated service delivery for stable ART patients [18]. The study protocol was developed using the Standard Protocol Items: Recommendations for Interventional Trials (SPIRIT) Checklist (see Additional file 1) and adheres to the SPIRIT recommendations. Each arm will consist of 10 clusters (health facilities) as follows:Control arm: participants will receive ART at 3-month intervals provided at the facility (arm 3MF)Intervention arm 1: participants will receive ART at 3-month intervals provided in CARGs (arm 3MC)Intervention arm 2: participants will receive ART at 6-month intervals provided in CARGs (arm 6MC)

### Outcomes and hypotheses

The rationale for the control arm selection is that provision of ART refills 3-monthly at the facility is the most established standard of care option for stable ART patients in Zimbabwe. All outcomes will be compared between all three arms. The primary outcome is participant retention in care, defined as the proportion of participants remaining in care 12 months after enrollment by intention-to-treat. Retention in HIV care is one of the most important determinants of the overall impact of ART [21]. Retention in care will also be compared after 24 months.

The principal hypotheses are that participant retention in both the intervention arms will be non-inferior to retention in the control arm with a non-inferiority margin of − 3.25% (risk difference). An additional hypothesis is that retention in intervention arm 6MC will be non-inferior to retention in intervention arm 3MC. The rationale for the non-inferiority design is that we anticipate retention to be at least similar in the intervention arms vs. control, and anticipate that provider (and participant-level) costs will be lower in the intervention arms vs. the control due to reduced participant contact with healthcare facilities in the intervention arms. If clinical outcomes in the intervention arms are at least non-inferior compared to the control arm, the interventions are anticipated to show cost savings compared to the control.

The secondary outcomes are:I.The proportion of participants achieving virological suppression 12 and 24 months after study enrollmentII.The proportion of participants retained in the study model of care after 12 and 24 monthsIII.Average annual cost per participant from a provider perspectiveIV.Average provider cost per participant retained, and average provider cost per participant retained with virological suppression 12 and 24 months after enrollmentV.Average annual participant-level expenditure to access treatmentVI. Qualitative research to assess the acceptability of multimonth dispensing (MMD) of ART within CARGs from both a participant and healthcare provider perspectiveVII. Site-level indicators of potential facility-level decongestion during the study. These are:Median difference in facility patient waiting times after 12 and 24 months compared to baselineTrend in the monthly number of patients newly initiated on ARTTrend in the monthly number of patients who receive provider-initiated HIV counseling and testing at the clinic

### Definitions

The primary outcome of retention in care will be defined as 1-participant attrition, where attrition is defined as either death (all-cause) or loss to follow-up (LTFU). LTFU will be defined as no facility or ART collection for > 90 days after the last missed scheduled ART collection [22, 23]. (Participants not arriving for the 12- or 24-month visit will be considered retained at these time points if collecting ART in person within 90 days of the scheduled appointment date). Participants with documented transfers to another clinic will be considered retained at the next immediate time point (12 or 24 months), and will then be censored. For the secondary outcome of retention in the study model of care, participants will be considered non-retained if transitioning off the study arm for any reason, including death, LTFU, change in ART-dispensing frequency, incident comorbidity requiring more frequent clinic visits, personal preference or withdrawal of consent to participate. Reasons for a change in ART-dispensing frequency include incident opportunistic infections, drug toxicity requiring closer monitoring, provider judgment based on change in clinical status or inadequate adherence, viral load > 1000 copies/ml, or pregnancy. Viral suppression will be defined as a viral load < 1000 copies/ml.

### Description of interventions

The study implementing partners employing the CARG model will align to the routine Zimbabwe CARG model [24], with adaptations to allow for extended ART-dispensing intervals. CARGs consist of 6–12 people, and CARG participants live in a similar geographic location and attend the same health facility. Participants at facilities in the 3MC and 6MC arms will be enrolled from newly formed CARGs (under 3 months) in which members have not had their first CARG-refill meeting. These CARG members will receive a viral-load test to ascertain stability and eligibility for the study. A CARG leader will be nominated, and the CARG will meet on at least a 3-monthly basis at a venue of their choice to access treatment. They may meet more regularly pending the group need for adherence support or to address psychosocial barriers to adherence. Stable study participants will have a clinical consultation and viral-load test at the facility at least annually after enrollment. Thus, after 12 months and 24 months, the entire CARG will be required to report to the facility on the same day. Each CARG member will collect their own ART supply on this day. For the 3MC arm, a single, alternating CARG representative will report to the facility after 3, 6, 9, then 15, 18 and 21 months to collect a 3-month supply of ART for all members of the CARG. This CARG representative will distribute the medicines to the other CARG members at the CARG meeting on the same or the following day. For the 6MC arm, a single CARG representative will report to the facility at 6 months and again after 18 months to collect a 6-month ART supply for all members of the CARG. Each CARG will be supplied with a back pack or small wheeled suitcase to carry medicines. Participants in the control arm (3MF) will receive their own supply of ART collected 3-monthly at the facility, and will receive annual clinical consultations.

### Setting and site selection

The study facilities are public health facilities located in Chitungwiza municipality, Masvingo and Matebeleland South provinces and Mberengwa district. These areas are representative of high-HIV-burden districts prioritized for scale-up of HIV services with increased support from the US President’s Emergency Plan for AIDS Relief (PEPFAR), and health facilities in these areas have prioritized the implementation of CARGs. Chitungwiza municipality is an urban local authority situated about 25 km south of the capital city, Harare. Masvingo and Matebeleland South are predominantly rural provinces located in the south-eastern and south-western regions of Zimbabwe, respectively, while Mberengwa is a rural district in Midlands province.

We selected 30 facilities from the study districts according to the following site selection criteria: (1) supply-chain procedures for implementation of MMD of ART at the site were deemed to be feasible by the facility managers and MOHCC, (2) implementation of CARGs were deemed to be feasible or had recently been implemented, (3) routine site-data collection systems were adequate and (4) at least 430 adults were receiving ART (to fulfill site sample-size requirements).

### Cluster allocation

Figure 1 illustrates the cluster allocation schema. To produce balance in urban and rural facilities as well as hospitals and clinics between the arms, a restricted randomization using three strata has been conducted [25], i.e., urban facilities (six facilities); rural hospitals (12 facilities) and rural clinics (12 facilities). One large rural clinic which has a large patient load similar to the rural hospitals, and which is currently applying to become a hospital, will be considered a hospital for the study. Following the stratified randomization, each arm consists of two urban facilities, four rural hospitals and four rural clinics. Cluster randomization has been conducted by an independent statistician using random-number generation with Microsoft Excel®.

**Fig. 1 Fig1:**
[figure not shown]
Cluster allocation schema of multimonth dispensing of antiretroviral treatment cluster-randomized trial in Zimbabwe. *CARGs* community antiretroviral treatment-refill groups

### Participant eligibility criteria

Participant eligibility will be aligned to those for stable ART patients in routine settings in Zimbabwe [24], and are shown in Table 1.

**Table 1 Tab1:** Inclusion and exclusion criteria for study participants

Inclusion criteria	Exclusion criteria
18 years of age or older	ART toxicity or tolerability issues in the prior 6 months
Confirmed HIV-1 infection based on the Zimbabwe national HIV-testing algorithm	Treatment for an opportunistic infection in the prior month
Received standard first-line ART for 6 months or longer	Receiving alternative first-line or second-line ART regimen
Viral load < 1000 copies/ml at enrollment	Active or suspected opportunistic infection
Weight ≥ 35 kg	Active or suspected tuberculosis
Willing to join a CARG	Comorbidities requiring more frequent visits to the facility than that required by the model of care
Provide informed consent for inclusion in the study	Confirmed pregnancy
	Less than 18 months postpartum

*ART* antiretroviral treatment, *CARG* community antiretroviral treatment-refill group, *HIV* human immunodeficiency virus

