### Recruitment and enrollment procedures

Figure 2 illustrates the overview of time schedules for enrollment, interventions and assessments according to SPIRIT. During the enrollment period, study nurses will screen all patients arriving for ART-refill visits at the study facilities and patients in recently formed CARGs according to the eligibility criteria. Potentially eligible patients will be invited by the study nurses to participate in the study, and to receive viral-load testing. It is not mandatory for all patients in a CARG to participate in the study. Eligible patients at each site who provide informed consent and who have a viral load < 1000 copies/ml will be enrolled until the facility enrollment cap has been reached. All study participants at a particular facility will receive the same model of care based on the arm to which that facility has been allocated. Patients already in CARGs at facilities in the control arm at the commencement of the study will not be considered for recruitment, and they will continue to receive care in CARGs as per the national guidelines similar to those in the 3MC arm.

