### Participant follow-up

All participants will be followed up for 24 months. As retention in care is the primary outcome, there will be no involvement regarding defaulter tracking beyond which exists routinely at each facility. Viral-load testing will occur at annual intervals, according to national guidelines [18]. Participants who become pregnant, develop tuberculosis or other opportunistic infections, have unsuppressed viral loads (≥1000 copies/ml), or who become clinically unwell will require clinic follow-up visits more frequently than 3-monthly as per national guidelines, thus they will transition off the study arm. These participants will remain under observational follow-up for the remainder of the study period for ascertainment of the primary outcome. CARG participants will return to be followed up at the facility. Frequency of ART-dispensing and clinical management will then be determined based on clinician assessment and national guidelines.

As Zimbabwe is moving to have ART refills provided in CARGs as an additional option for stable ART patients at all facilities [18], participants in the 3MF arm will be consigned to receive ART 3-monthly supplied at the facility for 12 months after enrollment; thereafter, participants will be offered the option of forming CARGs that receive ART 3-monthly. Participants who decline to join CARGs will continue to be followed up as arm 3MF for a further 12 months. This design was chosen taking into account program implementation plans for PEPFAR partners as they prioritize the roll-out of CARGs. It will allow arm 3MF to have at least 12 months of follow-up time to analyze retention and virologic suppression. After 24 months, all participants will receive nationally applied standard of care as at the time of study completion.

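### The comorbidity exclusion is tied to the arm's own visit schedule, so as written it can admit different patients to 3MF than to the CARG arms after facilities have been randomised

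*Protocol article*

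**What the plan says.** All references are to the protocol article.

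- **Participant eligibility criteria, Table 1.** One exclusion reads "Comorbidities requiring more frequent visits to the facility than that required by the model of care". No number of visits is given.
- **Recruitment and enrollment procedures.** The model of care belongs to the arm: "All study participants at a particular facility will receive the same model of care based on the arm to which that facility has been allocated".
- **Description of interventions.** For the control arm: "Participants in the control arm (3MF) will receive their own supply of ART collected 3-monthly at the facility, and will receive annual clinical consultations". For 3MC, apart from the whole-group visits at 12 and 24 months, "a single, alternating CARG representative will report to the facility after 3, 6, 9, then 15, 18 and 21 months". For 6MC, "a single CARG representative will report to the facility at 6 months and again after 18 months to collect a 6-month ART supply". For clinical review, "Stable study participants will have a clinical consultation and viral-load test at the facility at least annually after enrollment".
- **Cluster allocation.** Facilities are already assigned: "Cluster randomization has been conducted by an independent statistician". Study design describes the trial as unblinded.
- **Participant follow-up.** Participants with certain new events "will require clinic follow-up visits more frequently than 3-monthly as per national guidelines, thus they will transition off the study arm". This is a single frequency for all arms.

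**The concern.** In a cluster trial, randomising facilities makes the patients at those facilities comparable in expectation. It makes the enrolled participants comparable only if the same entry rule is applied in every arm. Here one rule takes its threshold from the arm, and the nurses who apply it know the arm.

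The patients affected are those whose comorbidity needs facility visits more often than a CARG member attends but no more often than 3-monthly. Patients needing visits more often than 3-monthly are excluded from all three arms.

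Two sets of results are exposed. The first is 12-month retention, judged against a 3.25-point margin. The second is provider cost, which includes outpatient and inpatient care, drugs and laboratory tests. If 3MF alone takes patients with regularly reviewed comorbidities, its cost per participant would tend to be higher for a reason unrelated to the delivery model.

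**Working it through.** **Step 1: the rule applied in each arm.** Take a patient with a comorbidity needing a facility visit every 3 months who meets all other criteria. The article does not define visit, so three readings are tried.

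| Reading of visits required by the model of care | 3MF | 3MC | 6MC |
|---|---|---|---|
| Participant's own attendance at the facility | 3-monthly: eligible | about annual: excluded | about annual: excluded |
| Refill interval of the model | 3-monthly: eligible | 3-monthly: eligible | 6-monthly: excluded |
| Clinical consultation only | annual: excluded | annual: excluded | annual: excluded |

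Own attendance in the CARG arms is the annual visit plus occasional turns as representative. The first reading affects both principal comparisons with 3MF. The second affects 6MC against 3MF and the additional comparison of 6MC with 3MC. Only the third removes the asymmetry, and the article does not state it.

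**Step 2: the plan's own figure.** Inputs from Sample size estimation: retention 95% in both arms, intracluster correlation 0.01, 192 participants per facility, margin 3.25 points, one-sided alpha 0.05. Study design gives 10 facilities per arm.

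- Design effect = 1 + (192 − 1) × 0.01 = 2.91
- SE = √(2 × 0.95 × 0.05 × 2.91 / 1920) = 0.0120, or 1.20 points
- Power = Φ(0.0325 / 0.0120 − 1.645) = 85.6%, against 85% stated. The figure reproduces, so this SE is used below.

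**Step 3: how a difference in case mix becomes bias.** Let q be the extra share of such patients in 3MF, and d the shortfall in their 12-month retention relative to other participants. Control retention is then lowered by q × d, and the observed difference moves by that amount towards the CARG arms. The article gives neither q nor d. Both are assumptions here: q from 5% to 20%, d from 3 to 10 points. Each case also assumes that the CARG arms enrol none of these patients.

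The analysis plan declares non-inferiority when the lower 95% confidence limit exceeds −3.25%. Taking the interval as two-sided, the false non-inferiority rate at the margin is Φ(−1.96 + bias / SE).

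| q | d (points) | Bias q × d (points) | Share of margin | False non-inferiority |
|---|---|---|---|---|
| none | none | 0 | 0% | 2.5% |
| 5% | 3 | 0.15 | 5% | 3.3% |
| 10% | 5 | 0.5 | 15% | 6.1% |
| 20% | 5 | 1.0 | 31% | 13.0% |
| 20% | 10 | 2.0 | 62% | 38% |

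This SE uses 95% in both arms. At the margin the intervention arm is at 91.75%, so SE = √((0.95 × 0.05 + 0.9175 × 0.0825) × 2.91 / 1920) = 0.0137. Biases of 0.5 and 1.0 point then give 5.5% and 11.0%, much the same.

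**Step 4: the opposite sign.** If these patients are retained better, d is negative. A bias of −0.5 point lowers the false non-inferiority rate to Φ(−1.96 − 0.005 / 0.0120) = 0.9%. It also lowers power under the 95% interval rule, when the arms truly do not differ, from Φ(0.0325 / 0.0120 − 1.96) = 77% to Φ(0.0275 / 0.0120 − 1.96) = 63%.

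**The case against.** **A common threshold may have been meant.** Annual consultations are planned in every arm, and the extra 3MF contacts are drug collections. Table 1 is a single list aligned to national criteria for stable patients, and it requires even control participants to be willing to join a CARG. This is a fair reading of intent and may be how some sites apply the rule. It is not what the criterion says, and 30 facilities are left to interpret it.

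**Healthier CARG arms by design.** A reader might infer that the rule makes the intervention arms healthier and so favours non-inferiority. The article does not support that. Nothing in it says patients with reviewed comorbidities are retained less well. The definition of loss to follow-up could even work in their favour, since a patient with another reason to attend has more chances of a qualifying contact. The common exclusions (viral load, opportunistic infection, tuberculosis, recent toxicity, regimens other than standard first-line) also limit any excess attrition. This objection stands: direction is unknown and size undocumented.

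**A contradiction with the follow-up rule.** A reader might also infer that entry and exit rules flatly conflict. The follow-up text concerns events arising during the study, such as pregnancy, tuberculosis or viraemia, while Table 1 concerns comorbidities at entry. The mismatch is loose: one uses a common frequency, the other does not.

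**Planned adjustment.** The analysis plan adjusts for imbalanced baseline variables. This helps only if comorbidity visit need is recorded. Where a group is excluded by rule from one arm there is no overlap, and a regression model can only extrapolate.

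**Conclusion.** The point holds as a fault in the wording of the entry rule that permits selection to differ by arm after randomisation. Under the plainest reading it affects both CARG arms; under the refill-interval reading it affects 6MC only; it disappears only under a reading that the article does not state.

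How much it matters cannot be derived from the article. Under assumed shares of 5% to 20% and retention shortfalls of 3 to 10 points, the bias is 0.15 to 2.0 points towards the CARG arms, and the upper end needs both extremes together. The middle case, 0.5 point, takes the false non-inferiority rate from 2.5% to about 6%. With the opposite sign the trial loses power instead. The provider-cost comparison is exposed whichever way retention goes. This merits correction and a prespecified check; it does not show that the primary comparison is invalid.

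**What to change.** 1. Reconcile Table 1 with Description of interventions, Recruitment and enrollment procedures, and Participant follow-up, so that one visit-frequency criterion, independent of arm, applies identically at all 30 facilities. State whether visits means attendance, refill or clinical review. The clinical level is for the sponsor to set.
2. For participants already enrolled, extract comorbidity visit need at baseline from the patient files, which are already a source document, and report it by arm.
3. Prespecify a sensitivity analysis of retention and provider cost restricted to participants who would have been eligible in every arm.

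The cost is a short amendment, extra data extraction and one further analysis; some 3MF candidates may become ineligible. Recruitment was expected to end around December 2017 and the article appeared on 29 January 2018, so the amendment may reach few enrolments. Items 2 and 3 therefore matter most.
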